### Statistical Analysis

Continuous variables with normal distribution will be reported as mean and standard deviation, while those with nonnormal distribution as median and interquartile range. Categorical variables will be expressed as frequencies and percentages. Continuously data collected will be explored for normality assumption by means of a Shapiro-Wilk test to calculate the appropriate descriptive statistics [47].

Repeated measured analysis of variance or Friedman test will be used to assess changes on continuous data with normal and nonnormal distribution, respectively, between baseline, follow-up, and end-of-study visits. Possible associations between variables will be investigated using Pearson or Spearman correlation coefficients. We estimated sample size conducting power analysis using G*Power software (version 3.1). We performed repeated measures analysis of variance (3 time conditions) using 80% power, a medium effect size of 0.25, and significance level of 5%. The sample size was estimated to be 28 participants. One-third of this patient population that will agree to proceed to home study (phases 1 through 3) will enter the next steps of study protocol [48]. All statistical analyses will be performed using SPSS Statistics version 23.0 (IBM Corp) or R for Windows version 3.1.3 (R Foundation for Statistical Computing).

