### At-Home Study Design

#### General Design

BioTechCOACH-ForALL home study is a prospective, multiple baseline across subjects, nonrandomized, single-arm, single-center study following a within-subject design to assess the feasibility and efficacy of the Virtual Coach Program in older age patients with HF. The study will be delivered in three phases, each of them fulfilling a different scope. All participants will go through all study phases. Each phase will allow participants to familiarize themselves with the delivered technology of that phase. A multiple baseline approach will be followed so that the effects of each phase are as isolated to the previous phases as possible, allowing for effect comparison among them. Clinical and quality of life assessment and exercise behavior and attitude will be measured repeatedly in both the baseline phase and the two intervention phases. This way any cause-effect relationships among the intervention and patient outcome measures will be demonstrated.

The study conforms to the ethical guidelines of the 1975 Declaration of Helsinki, all participants will sign informed consent, and the study protocol has been approved by the bioethics committee of the School of Medicine of the Aristotle University of Thessaloniki (Protocol No. 1.45/21.11.2018) and registered at ClinicalTrials.gov [NCT03877328]. The study protocol is structured in a manner that incorporates three different phases, coming one after the other. Each patient will enter the study in the phase 1 and complete their participation in phase 3.

#### Phase 1

Phase 1 introduces the objective measurement technology, the wearable monitoring device. This technology will be running throughout the project’s lifetime and will provide objective information on patient activity. This information, along with the doctor’s baseline and intermediate assessment, will be used as an indicator of the effectiveness of phases 2 and 3.

#### Phase 2

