### Clinical Assessment

Patients will be clinically evaluated before entering each of the two studies and on the initiation of each protocol phase (meaning before entering phase 1, phase 2, and phase 3, and at the end of phase 3, which will mark the end of study), completing 4 on-site clinical visits for the impact of each intervention to be assessed.

On the baseline, intermediate, and follow-up assessments, patient clinical condition, quality of life, and health-related costs will be considered. More specifically, blood pressure, heart rate, blood oxygen saturation, and body weight will be measured for the clinical assessment. To assess physical status, the 6-minute walk test and NYHA functional class will be used for exercise intolerance. Patient-related outcomes to be used include the Beck Depression Inventory [42] and the Dukes questionnaire [43]. As for the evaluation of quality of life, the Short Form Health Survey questionnaire [44,45] will be employed. Self-efficacy for exercise behavior scale will be used for evaluation of changes in patient perspectives on exercise [46]. Finally, for health-related costs, the effect on number of hospital admissions along with the effect on health care use (number of primary and secondary care contacts, social care contacts, relevant medication use) will be calculated during all three phases.

Real-world data will be collected continuously (across all phases of the home study) to assess several aspects of the interventions planned. Continuously measured activity levels expressed in daily steps taken by the patient will be compared across the different study phases. Real-life adherence of the HF patients to the proposed intervention will be measured in terms of attendance at the webFitForAll platform using wearable heart rate monitoring data as well as online activity logs and telephone and clinic follow-up. Real-world adherence will be compared within-subjects for the second and third phases of the study. Use analytics (virtual coach used, content and delivery time of messages/recommendations) of the e-coaching system and juxtaposed relevant outcomes (such as activity levels collected by the activity tracker and adherence to the webFitForAll training program given any system logs) will be routinely collected. Patients adherence will be evaluated by measuring attendance at the webFitForAll and heart rate monitoring data as well as by activity logs and telephone and clinic follow-up.

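### Roughly six to ten continuous outcomes are tested with none named as primary; the only stated level (5%) and power (80%) describe one unnamed test, yet the article sets an efficacy aim and promises demonstrated effects

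*Protocol article*

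**What the plan says.** **Test rule (Statistical Analysis).** "Repeated measured analysis of variance or Friedman test will be used to assess changes on continuous data with normal and nonnormal distribution", between the baseline, follow-up and end-of-study visits. No outcome is singled out.

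**Outcomes (Clinical Assessment).** Four clinical measures are taken: blood pressure, heart rate, oxygen saturation and weight. The section adds 6-minute walk distance, then "Patient-related outcomes to be used include the Beck Depression Inventory" and the Dukes questionnaire, the Short Form survey and a self-efficacy scale for exercise. For the wearable data, "Continuously measured activity levels expressed in daily steps taken by the patient will be compared across the different study phases". Adherence is compared between phases 2 and 3 only. No outcome is labelled primary or secondary.

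**Level and power (Statistical Analysis).** "We performed repeated measures analysis of variance (3 time conditions") was the model, "using 80% power, a medium effect size of 0.25, and significance level of 5" per cent, and "The sample size was estimated to be 28 participants". The calculation names no outcome. The same paragraph says that one-third of these patients go on to the home study.

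**Claim (At-Home Study Design, General Design).** The home study is to assess feasibility and efficacy, and "This way any cause-effect relationships among the intervention and patient outcome measures will be demonstrated".

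**The concern.** A 5% level and 80% power mean something only for an identified test. Here they belong to one test of an unnamed outcome, while the analysis rule covers a whole list and the claim reaches across the patient outcome measures. A reader of the eventual results could not tell which one was meant to decide whether the program made patients more active. If one favourable result out of many can be presented as evidence of efficacy, the risk of a false claim is well above the only error rate that the article states.

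**Working it through.** **1. Reproduce the stated sample size.** Inputs from Statistical Analysis: m = 3 conditions, f = 0.25, alpha = 0.05, power 80%. The correlation between repeated measures and the sphericity correction are not stated; I assume rho = 0.5 and epsilon = 1.

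- Noncentrality: lambda = N × m × f² / (1 − rho) = 28 × 3 × 0.0625 / 0.5 = 10.5.
- Degrees of freedom: m − 1 = 2 and (N − 1)(m − 1) = 54.
- Power = 0.812, and 28 is the smallest N that reaches 80%. The stated figure is reproduced.
- Other values of rho give N = 53 (rho 0), 38 (0.3) and 17 (0.7). Four time points at rho 0.5 give 24.

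So 28 is the size for one three-condition test at an unadjusted 5%.

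**2. Count the outcomes.**

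- Ten: blood pressure, heart rate, oxygen saturation, weight, 6-minute walk, Beck, Dukes, Short Form, self-efficacy, daily steps.
- Six: the same list without the four clinical measures, which may serve safety more than efficacy.

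**3. Chance of at least one false positive.** This assumes that every null hypothesis is true, that each outcome is tested at 5%, and that any significant outcome may support efficacy. Under independence the chance is 1 − 0.95^K:

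- K = 6: 1 − 0.735 = 0.265.
- K = 10: 1 − 0.599 = 0.401.

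Outcomes from the same patients are correlated, so these are upper figures. Simulated repeated-measures ANOVAs (ten outcomes, three time points, 20,000 replicates, equal correlation between outcomes) gave nearly the same results for 10 and for 28 patients:

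| Between-outcome correlation | At least one false positive, ten outcomes |
|---|---|
| 0 | 40% |
| 0.3 | 35-36% |
| 0.5 | 30% |
| 0.7 | 22-24% |
| 0.8 | 18-19% |

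The correlated case was not simulated for six outcomes; it lies below 26.5%.

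**4. Power in the home study.** One-third of 28 is 9.3, so 9 to 10 patients. With f = 0.25, rho = 0.5 and alpha = 0.05:

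- N = 9: lambda = 9 × 3 × 0.0625 / 0.5 = 3.375; power 0.302.
- N = 10: lambda = 3.75; power 0.338.

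**5. Would adjusting over all ten outcomes be better?** Bonferroni at 0.05 / 10 = 0.005 needs N = 45 for 80% power and leaves about 50% at N = 28. With 9 to 10 patients, power is about 7-9%. One primary outcome is the more workable route.

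**The case against.** The strongest reply is that the inflation rests on a decision rule that the article never writes. It nowhere says that one significant outcome is enough, and 5% appears only in the sample-size sentence. The causal sentence in General Design refers to the repeated-measurement design, not to p values. All of this is correct. A reader might infer that the plan promises an overall 5% error rate and breaks it, or that its false-positive rate is 40%. The documents support neither: no overall rate is claimed, and 40% combines the longest list with zero correlation.

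The count can also be challenged. The four clinical measures are taken for clinical assessment, and the Discussion links the evaluations before each phase to patient safety. Steps are compared by phase, whereas the test rule speaks of visits. This is why the range starts at six outcomes and why tests across visits or phases are counted together.

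A formal multiplicity procedure may sit in a full protocol or analysis plan that is not shown, so its absence here is no finding. The home study is also called a pilot and a single-case series, which would soften the point if its results were described as exploratory.

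Finally, the article is not silent about priorities. Its objectives name adherence and a more active lifestyle, and Wearable Monitoring says that activity data will evaluate the interventions against baseline. That shows which outcome is the natural choice; it does not make the choice or link it to the test.

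What remains is in the published text: a power calculation for one unidentified outcome, beside an efficacy aim and a promise that extend over the outcome measures.

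**Conclusion.** The point holds in a limited form. Roughly six to ten continuous outcomes are compared with none ranked, and the stated level and power belong to a single unnamed test. If each is tested at 5% and any significant one may support efficacy, the false-positive risk is at most about 27% to 40% under independence. With correlation it is lower, but in every case simulated for ten outcomes it remained above three times 5%.

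Two stronger inferences should be resisted. First, naming daily steps as primary would not give it 80% power with 28 patients. Steps are collected only in the home study, and on the one-third figure power is about 30-34% at rho = 0.5. Second, controlling multiplicity would not justify the causal promise. The study is single-arm and nonrandomized, which limits that claim whatever the number of tests.

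**What to change.** 1. In Clinical Assessment and Statistical Analysis, name mean daily steps per phase, compared over phases 1 to 3, as the single primary efficacy outcome, tested at 5%. The article already uses activity to evaluate the interventions, and three phases match the three conditions of the power calculation better than the four clinic visits do.
2. Report adherence and all other outcomes as estimates with 95% confidence intervals, without confirmatory significance claims.
3. In General Design, change the causal sentence so that effects are to be estimated, not demonstrated.
4. Do not attach 80% power and N = 28 to steps. Either state the power for the number actually entering the home study (about 30-34% for f = 0.25 with 9 to 10 patients, with the assumed correlation of 0.5 written down), or describe the home-study analysis as exploratory.

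The cost is wording, with no new measurements. The downsides are that fewer outcomes can be called significant and that the stated power is less favourable. The article reports phases 2 and 3 as not yet complete, so the choice can be recorded and dated before the final outcome data exist.

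### Four clinical visits are scheduled, but the analysis names three and does not say which, so the visit-based outcomes may not give a separate change for each phase

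*Protocol article*

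**What the plan says.** The Clinical Assessment section places the visits "before entering phase 1, phase 2, and phase 3, and at the end of phase 3, which will mark the end of study", with each patient "completing 4 on-site clinical visits for the impact of each intervention to be assessed". The next paragraph of that section refers to them with three labels: "On the baseline, intermediate, and follow-up assessments".

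The Statistical Analysis section says "Repeated measured analysis of variance or Friedman test will be used to assess changes on continuous data", and gives the comparison as "between baseline, follow-up, and end-of-study visits". The sample size rests on "repeated measures analysis of variance (3 time conditions"), "using 80% power", "a medium effect size of 0.25" and a 5% significance level, giving 28 participants. About one-third of these go on to the home study.

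The General Design section describes a single-arm, within-subject study that aims to isolate the effect of each phase from the earlier ones so that the phases can be compared. The Clinical Assessment section also compares daily steps across phases, and adherence between phases 2 and 3.

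**The concern.** Call the visits V1 (before phase 1), V2 (before phase 2), V3 (before phase 3) and V4 (end of phase 3). Each phase lies between two neighbouring visits. V2−V1 is the change under wearable monitoring alone, V3−V2 the change under exergames, and V4−V3 the change once e-coaching is added. The study has no control group, so V2−V1 is the only view of drift and test learning in the visit-based outcomes.

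The analysis names three visits. The labels do not show which, because *follow-up* comes last in the Clinical Assessment list and in the middle of the Statistical Analysis list. If the analyst fits three levels, at least one phase change is no longer estimated on its own. The choice of visits is also left open until the data are in hand.

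**Working it through.** **1. Inputs.** Four visits and their timing come from Clinical Assessment. The three named visits, three time conditions, effect size 0.25 (read as Cohen's f), 80% power, 5% level, N = 28 and the one-third share come from Statistical Analysis. The article gives neither the correlation between measurements (rho) nor the sphericity factor (epsilon). I assume rho = 0.5 and epsilon = 1 and show a range.

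**2. What three levels can estimate.** Four visits bound three intervals; three levels bound two. V4 is the end-of-study visit on any reading.

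| Levels used | First change | Second change | Consequence |
|---|---|---|---|
| V1, V3, V4 | V3−V1 | V4−V3 | monitoring merged with exergames |
| V1, V2, V4 | V2−V1 | V4−V2 | exergames merged with e-coaching |
| V2, V3, V4 | V3−V2 | V4−V3 | both interventions separate; no-intervention change lost |
| V1, mean of V2 and V3, V4 | (V2−V1) + half of (V3−V2) | (V4−V3) + half of (V3−V2) | exergame effect split over both changes |
| mean of V1 and V2, V3, V4 | (V3−V2) + half of (V2−V1) | V4−V3 | interventions separate from each other; half of the phase 1 change stays in the exergame estimate |

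No row gives all three phase changes.

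**3. The plan's own sample size.** For a one-group repeated-measures F test with m measurements and epsilon = 1, lambda = f²·n·m/(1−rho), df1 = m−1 and df2 = (n−1)(m−1).

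- m = 3, n = 28: lambda = 0.0625 × 28 × 3 / 0.5 = 10.5, df 2 and 54, power 81.2%. With n = 27 it is 79.6%. The stated 28 reproduces.
- m = 4, n = 24: lambda = 0.0625 × 24 × 4 / 0.5 = 12.0, df 3 and 69, power 81.7%. With n = 23 it is 79.7%.
- m = 4, n = 28: lambda = 14.0, df 3 and 81, power 88.0%.

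At epsilon = 1, the required N for rho 0.3, 0.5 and 0.7 is 38, 28 and 17 with three measurements, and 32, 24 and 15 with four.

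**4. Illustration of misattribution.** One-third of 28 is 9.3, so n = 9. Assume SD 1 at each visit, equal correlation rho, and a two-sided 5% paired t test (noncentral t, 8 df).

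- V2 and V3 pooled, e-coaching without effect, exergame effect 0.5 SD. The contrast V4−(V2+V3)/2 has mean 0.5/2 = 0.25 in absolute size and SD √(1.5(1−rho)) = √0.75 = 0.866. Noncentrality is 0.25/0.866 × √9 = 0.87, and the contrast is significant in 12% of studies (10% to 17% for rho 0.3 to 0.7).
- V2 dropped, exergames without effect, phase 1 change 0.3 SD. The contrast V3−V1 has mean 0.3 and SD √(2(1−rho)) = 1. Noncentrality is 0.3 × 3 = 0.90, and the contrast is significant in 13% (10% to 18%).

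**The case against.** The strongest reply is that the three labels may be categories and not factor levels. Clinical Assessment itself uses three labels for its four visits, so *follow-up* in the analysis sentence may loosely cover both middle visits. Repeated-measures ANOVA and the Friedman test both accept four levels without a change to that sentence. Nothing in the article says that a visit is discarded or that two are averaged. This stands as a possible reading, but the article does not state it, and the power line again says three.

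A second reply is that General Design speaks of a baseline phase and two intervention phases. With V2 as baseline, exergames and e-coaching stay separable and only the no-intervention change goes. This also stands. A reader might infer that one phase's effect must be lost or credited to another intervention; the text does not support that much.

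A reader might also infer that the study is too small because of the mismatch. It is not: a fourth measurement lowers the required number. Nor should the illustration be run at n = 28, where it gives 31% and 33%, because Statistical Analysis sends only about one-third of the 28 to the home study.

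Finally, the project's main aims are exercise adherence and a more active life. Steps and adherence are compared by phase and do not depend on the three-visit wording. *3 time conditions* may well mean the three phases, but the article does not say so.

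**Conclusion.** The mismatch is real and should be fixed. The schedule gives four visits; the analysis and the power calculation give three, with inconsistent labels and no mapping between them. On a three-level reading, the visit-based outcomes cannot yield all three phase changes, and which one is merged or lost depends on a choice the article leaves open.

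The size of the consequence is conditional. The 12% and 13% against a nominal 5% rest on assumed effects (0.5 SD and 0.3 SD), on rho = 0.5, on about 9 patients, and on pooling or dropping a visit, which the article does not state. If V2 is the intended baseline, or if all four visits enter as levels, neither figure applies. The flaw lies in the definition of the analysis, is confined to the visit-based outcomes, and does not call the figure of 28 into question.

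**What to change.** In Statistical Analysis, name the visits V1 to V4 and use the same labels in Clinical Assessment. Analyse the visit-based outcomes with visit as a four-level factor, by repeated-measures ANOVA or Friedman test as already planned. Report three contrasts: V2−V1 (no intervention), V3−V2 (exergames) and V4−V3 (e-coaching).

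For the power line, either state that the three time conditions are the three phases for daily steps, or rerun it with four measurements and give the assumed correlation and epsilon.

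The cost is a few sentences and at most one rerun of the calculation. All four visits are already scheduled, so no further data collection is needed.

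### Four clinical visits are scheduled to assess each phase, but the planned test and the power statement name three time points, so as written only two of the three phase changes can be estimated for visit-based outcomes

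*Protocol article*

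**What the plan says.** The Clinical Assessment section places the on-site visits "before entering phase 1, phase 2, and phase 3, and at the end of phase 3, which will mark the end of study", with patients "completing 4 on-site clinical visits for the impact of each intervention to be assessed". Call these V1, V2, V3 and V4. Phase 1 (wearable monitoring only) lies between V1 and V2, phase 2 (exergames) between V2 and V3, and phase 3 (e-coaching added) between V3 and V4.

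The General Design section gives the reason for this layout: the effect of each phase is to be separated from the phases before it, so that phases can be compared.

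The Statistical Analysis section assigns repeated-measures analysis of variance, or the Friedman test, to changes in continuous data "between baseline, follow-up, and end-of-study visits". The power analysis reads: "We performed repeated measures analysis of variance (3 time conditions) using 80% power, a medium effect size of 0.25", with a 5% significance level and a result of 28 participants. About one-third of these are to go on to the home study.

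Separately, the Clinical Assessment section says that daily steps will be compared across the study phases.

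**The concern.** The schedule has four measurement occasions, while the test and the power statement name three. The article does not say which scheduled visit is the baseline of the test, which is the follow-up, or whether one label covers two visits. It describes no other test for visit-based change.

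What is at stake is which effects can be estimated. The home study has one arm, and each patient serves as his or her own control. V1 to V2 is the only interval without exergames or e-coaching. It is therefore the only internal reference for change due to repeat testing or to wearing a monitor. V2 to V3 and V3 to V4 carry the two interventions. An analysis with one occasion fewer than the schedule cannot report all three intervals separately.

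**Working it through.** **1. Inputs.** From the Statistical Analysis section: 3 measurements, effect size 0.25 (read as Cohen's f), power 80%, alpha 5%, G*Power 3.1, result 28. From the General Design section: one group. From the Clinical Assessment section: 4 visits. Not stated in the article, and so assumed: correlation between measurements rho = 0.5 and sphericity factor eps = 1.

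**2. Formula** (repeated measures, within-subject factor, one group, m measurements, N patients):
- noncentrality = f² × N × m × eps / (1 − rho)
- df1 = (m − 1) × eps
- df2 = (N − 1) × (m − 1) × eps
- power = probability that the noncentral F exceeds the 5% critical value

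**3. The plan's own figure.** With m = 3 and N = 28, noncentrality = 0.0625 × 28 × 3 / 0.5 = 10.5 on 2 and 54 df, and power is 0.812. N = 27 gives 0.796. The smallest N is 28, an exact match, so the published figure is consistent with a three-measurement calculation under these assumptions.

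**4. The same calculation for the scheduled visits.** With m = 4 and N = 24, noncentrality = 0.0625 × 24 × 4 / 0.5 = 12.0 on 3 and 69 df, and power is 0.817. N = 23 gives 0.797. The smallest N is 24. At N = 28 the power would be 0.880. This holds f at 0.25 when the fourth occasion is added.

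**5. Range over the unstated inputs** (smallest N for 80% power):

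| rho | eps | m = 3 | m = 4 |
|---|---|---|---|
| 0 | 1 | 53 | 45 |
| 0.3 | 1 | 38 | 32 |
| 0.5 | 1 | 28 | 24 |
| 0.7 | 1 | 17 | 15 |
| 0.5 | 0.75 | 34 | 29 |
| 0.5 | lowest possible (1/2 for m = 3, 1/3 for m = 4) | 44 | 50 |

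**6. Number entering the home study.** 28 / 3 = 9.3, so about 9. With rho = 0.5 and eps = 1:
- m = 3: noncentrality = 0.0625 × 9 × 3 / 0.5 = 3.375, power 0.302
- m = 4: noncentrality = 0.0625 × 9 × 4 / 0.5 = 4.5, power 0.345

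**7. What three levels can estimate.** Three occasions give two successive changes. V4 is fixed as the end of study, so a three-level analysis leaves out one of the others:

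| Levels used | First change | Second change | What is lost |
|---|---|---|---|
| V2, V3, V4 | exergames | e-coaching added | monitoring-only change |
| V1, V3, V4 | monitoring and exergames together | e-coaching added | separation of monitoring from exergames |
| V1, V2, V4 | monitoring only | exergames and e-coaching together | separation of the two interventions |

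Each choice gives up part of the phase comparison that the design is meant to support.

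**The case against.** The best defence is that no sentence says a visit will be left out. The Clinical Assessment section itself describes its four visits with three labels (baseline, intermediate, follow-up), so three labels need not mean three levels. In the planned test, follow-up could cover both V2 and V3. This stands as a possible reading, but the power statement's three time conditions would then disagree with the test, and one of the two would still need correcting.

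Second, three conditions may mean three phases. For daily steps that is right and nothing is lost. But the Statistical Analysis section words its test by visits, and the walk test, questionnaires and vital signs are taken at visits.

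Third, with V2, V3 and V4 as the levels, exergames and e-coaching could still be separated and compared. This is correct. The loss would be the monitoring-only reference, not the whole comparison.

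Fourth, the limitations text announces analysis on an individual basis, so the group test is not the only route to phase effects. This is also correct, but it does not reconcile the group test with the schedule.

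Fifth, an omnibus test does not locate a change, but contrasts are commonly left to an analysis plan. Their absence is therefore not counted as an error here. Naming them is simply the natural way to complete the correction.

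A reader might go further and infer that V2 is dropped and any practice or monitoring effect is credited to the exergames. The article does not say which visit is omitted and gives no size for such effects, so that inference is not supported.

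**Conclusion.** The mismatch is real, and it is confined to visit-based outcomes. The schedule has four occasions, the planned test names three, and the sample size of 28 is reproduced exactly by three measurements and not by four (rho = 0.5 and eps = 1, both assumed). Read as three levels, two of the three phase changes can be estimated, and which two is not stated.

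A reader might infer that 28 is too small for four visits. The figures do not show that: under the same assumptions four measurements need 24. More than 28 would be needed only with a lower correlation or a marked departure from sphericity (for example 32 at rho = 0.3, or 29 at eps = 0.75).

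The low power at about 9 patients (0.302 with three levels, 0.345 with four) comes from the one-third share entering the home study and depends little on the number of levels. It is reported here because any restated power has to use that number.

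This is an inconsistency worth correcting before the phase comparisons are analysed. It does not invalidate the design.

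**What to change.** - In the Statistical Analysis section, name V1, V2, V3 and V4 as the four levels of the repeated-measures analysis of variance or Friedman test for visit-based outcomes. State separately that daily steps are compared over three phases.
- Prespecify three successive contrasts: V2 − V1 (monitoring only), V3 − V2 (exergames) and V4 − V3 (e-coaching added). Report V2 − V1 beside the other two as the reference.
- Do not subtract V2 − V1 from the later changes or scale it to phase length. The contrast V3 − 2V2 + V1 has squared coefficients 1 + 4 + 1 = 6, against 1 + 1 = 2 for V3 − V2. Under compound symmetry that is three times the variance. Scaling would also assume that the reference change grows linearly with time, and the article gives no length for phase 1.
- Restate the power for four measurements, with the assumed correlation and sphericity written down, and for the number expected to enter the home study.

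Cost: a few sentences, one power calculation, a decision on multiplicity for three contrasts, and a less favourable stated power. The four visits are already scheduled, and phases 2 and 3 are reported as still to be completed, so no new visits are needed.

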### Patient Population

Both studies can fulfill their objectives only if appropriate subjects are enrolled. The following eligibility criteria are designed to select subjects. These criteria must be met before a subject is assigned to the study. Subject eligibility should be reviewed and documented by a qualified member of the investigators’ study team before subjects are included in the study. All patients included in the study protocol will undergo all three home study phases, in addition to the EEG experiment in the lab. For the latter phase, a percentage of patients, without the need to proceed with the whole study protocol, will be recruited.

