### Intervention Setting

The first phase of the protocol will start in the 1st Department of Cardiology, AHEPA University Hospital of Thessaloniki, where all clinical assessments (6-minute walk test, questionnaires, clinical assessment, etc) will be completed, and it will continue in a dedicated area in the Laboratory of Medical Physics in the Faculty of Health Sciences of the Aristotle University of Thessaloniki, where patients will undergo the lab study/protocol. After the lab study, some of the patients will be included in the second study situated in their own homes, where they will keep performing their everyday activities. The physical training and e-coaching interventions (phases 2 and 3) will take place at patients’ homes as well.

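### The 80% power is stated for 28 participants, but the same paragraph sends about one-third of them into the home study, the only part with the repeated visits being compared

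*Protocol article*

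**What the plan says.** The Statistical Analysis section plans a repeated-measures ANOVA, or a Friedman test for nonnormal data, to assess change "between baseline, follow-up, and end-of-study visits". It bases the sample size on a repeated-measures ANOVA with 3 time conditions, "using 80% power, a medium effect size of 0.25, and significance level of 5" percent, run in G*Power 3.1. The result is given as "The sample size was estimated to be 28 participants". The next sentence is "One-third of this patient population that will agree to proceed to home study (phases 1 through 3) will enter the next steps" of the protocol.

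Other sections bear on how many patients reach the home study:

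- Intervention Setting: "After the lab study, some of the patients will be included in the second study situated in their own homes".
- Patient Population: "All patients included in the study protocol will undergo all three home study phases, in addition to the EEG experiment in the lab". The same paragraph ends by allowing a percentage of patients to be recruited who need not go through the whole protocol.
- Abstract, Results: the sample size is 28 for both studies, with 10 included so far and recruitment ongoing.
- Results: recruitment is complete, with 10 patients included.
- Clinical Assessment: four on-site visits, at the start of phases 1, 2 and 3 and at the end of phase 3.

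**The concern.** A power statement holds only for the number of patients who enter the analysis it describes. Here the number and the power are given for 28, and the following sentence takes about two-thirds of those patients out of the part of the project where repeated visits occur. A reader who takes the paragraph at face value would credit the home-study comparisons with 80% power.

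The General Design section says the home study assesses efficacy as well as feasibility, and expects cause-effect relationships to be demonstrated. If the home study has 9 or 10 patients, a non-significant change across phases says little about an effect of the size the study was planned for, and the article's only statement of sensitivity would suggest otherwise.

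**Working it through.** **1. Which analysis the calculation serves.** The article does not say so outright; this step is an inference. The calculation has time conditions. The visits in Clinical Assessment are tied to the home phases, so only home-study patients have the full series. The lab study contrasts stimulus conditions (age, gender, uniform) by topographic ANOVA and the SwE toolbox, and has no time conditions.

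**2. Inputs.** From Statistical Analysis: m = 3 time conditions, f = 0.25, alpha = 0.05, target power 80%. Assumed because not stated: within-subject correlation rho = 0.5 and sphericity (eps = 1), the G*Power defaults.

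**3. Formula** (one group, within-subject factor, noncentral F):

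- lambda = f² × n × m × eps / (1 − rho)
- df1 = (m − 1) × eps
- df2 = (n − 1)(m − 1) × eps

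**4. Reproducing the plan's figure.** At n = 28, lambda = 0.0625 × 28 × 3 / 0.5 = 10.5 with df 2 and 54, and power is 0.812. At n = 27, power is 0.796. The smallest n reaching 80% is therefore 28, as stated. Other inputs do not give 28: rho = 0.3 needs 38, rho = 0.7 needs 17, eps = 0.75 needs 34, and m = 4 needs 24.

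**5. Home-study number on the one-third reading.** 28 / 3 = 9.3, so about 9. The 10 patients reported in Results are taken as a second case.

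| n | lambda | df | Power at f = 0.25 | f detectable at 80% power |
|---|---|---|---|---|
| 28 | 10.5 | 2, 54 | 81.2% | (planned: 0.25) |
| 10 | 0.0625 × 10 × 3 / 0.5 = 3.75 | 2, 18 | 33.8% | 0.437 |
| 9 | 0.0625 × 9 × 3 / 0.5 = 3.375 | 2, 16 | 30.2% | 0.465 |

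A simulation under the same assumptions gave 0.814 at n = 28 and 0.305 at n = 9.

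**6. Sensitivity to the unstated inputs, n = 9, f = 0.25.**

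| Change | Power |
|---|---|
| rho = 0.3 | 22.6% |
| rho = 0.7 | 47.4% |
| rho = 0.8 | 65.3% |
| eps = 0.75 | 25.8% |
| m = 4 (all four visits) | 34.5% |

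A correlation of 0.9 would give 92.6% at n = 9, but the calculation would then have asked for only 7 patients, which does not fit the stated 28.

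**7. Precision at n = 9.** The 95% confidence interval for a mean paired difference has half-width t(0.975; 8) / √9 = 2.306 / 3 = 0.77 standard deviations of the paired difference.

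**The case against.** The strongest objection is that the article does not fix the home-study number at 9. The Abstract gives 28 for both studies, and General Design has all participants going through all phases. If 28 patients enter the home study, the stated power stands. The one-third sentence is also loosely worded: it may mean one-third of the 28, or one-third of those who agree. This stands, and it makes the power figure conditional. It does not clear the paragraph, because the one-third sentence and Intervention Setting both send only part of the group home, and the 10 patients in Results fit a similarly small number. One-third of those who agree would be no more than 9.

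A reader might infer that Patient Population flatly contradicts the one-third rule. The text does not support this. The paragraph's last sentence allows patients who do not go through the whole protocol, and it follows directly on the mention of the EEG experiment, so lab-only patients may be meant. The paragraph needs clarifying; the plainer conflict is with the Abstract.

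It is also fair that the link from the calculation to the home visits is inferred, and that 3 time conditions do not match 4 visits. The inference is strong for the reasons in step 1, and using four time points raises power at n = 9 only to 34.5%.

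Finally, the home study is already called a pilot in the Abstract, Results and Discussion. Strengths and Limitations describes a single-case series without a control group, analysed individually. That lessens the harm, but it does not make the 80% apply to 9 or 10 patients.

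**Conclusion.** The point holds in conditional form. As written, the 28 participants, the 80% power and the one-third rule cannot all apply to the comparison across home-study visits, and the article is inconsistent on how many patients that comparison will include.

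On the one-third reading, with rho = 0.5 and sphericity assumed, power at f = 0.25 is about 30% with 9 patients and 34% with 10. It runs from 23% to 65% at n = 9 for rho from 0.3 to 0.8. The effect detectable with 80% power is f of about 0.47 (n = 9) or 0.44 (n = 10), nearly twice the planned 0.25.

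A reader might conclude that the home study simply has 30% power. The article does not establish that: it also gives 28 for both studies, and neither the correlation nor the sphericity assumption is stated. What is established is that the 80% cannot be relied on for the home comparisons until the number is settled.

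**What to change.** State the number of home-study patients used for the visit and phase comparisons, and make the Abstract, Patient Population, Intervention Setting, Statistical Analysis and Results agree on it. This includes whether recruitment is ongoing or complete.

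- If the number is about 9 to 10: say that the 80% power does not apply to the home-study comparisons. Replace it with the achieved power or the detectable effect, and give the assumed correlation. Report changes between phases with 95% confidence intervals, and do not read a non-significant result as absence of effect.
- If all 28 are meant to enter the home study: delete the one-third sentence and correct Intervention Setting. The stated power then stands on the assumed inputs.

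In either case, align the 3 time conditions of the calculation with the 4 visits in Clinical Assessment, or say which three are compared.

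The cost is wording only and no extra patients. Under the first option the stated power becomes less favourable.
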